## Abstract

**Background:**

Alzheimer’s disease (AD) is characterized by cognitive impairment and behavioral impairment. The gait of AD patients is attracting the increasing attention. The aim of this randomized controlled trial (RCT) is to explore the effect of acupuncture on the cognitive function, gait performance, and hemodynamic changes in the prefrontal cortices.

**Methods:**

In this RCT, a total of 108 AD patients will be randomly assigned into acupuncture group or control group for 8 weeks. The primary outcome will be three-dimensional gait analysis and cerebral hemodynamics using functional near-infrared spectroscopy (fNIRS). Secondary outcomes will include Mini-Mental State Examination (MMSE), Montreal Cognitive Assessment (MoCA), and Barthel Index (BI).

**Discussion:**

This trial is expected to explore the effect of acupuncture on cognitive function, gait performance, and hemodynamic changes in the prefrontal cortices for AD patients.

## Introduction

Alzheimer’s disease (AD) is a degenerative disorder of the central nervous system, which is characterized by cognitive impairment and behavioral impairment (1). AD is the most common cause of dementia, and accounts for 60–80% of the cases globally (2). It is estimated that the number of AD patients will exceed 30 million, and about 50% of people over 80 years old will suffer from AD in China by 2050 (3). AD patients not only lose working ability, sociability, self-care ability, and quality of life, but also bring a heavy burden to their families (4).

Non-pharmacological interventions have been reported as the important choices for AD patients (1). Among the non-pharmacological interventions, 78% of patients in China select acupuncture-related treatments (5). Acupuncture has been used clinically in China for many years because of small wound, mild pain, and high security (6, 7). Studies have reported the efficacy of acupuncture in the improvement of cognitive impairment for AD patients (1, 8). Cognitive impairments are often associated with motor disorders, including bradykinesia, rigidity, balance, and gait disorders, which increases the risk of falls (9). The gait of AD patients has gradually attracted attention, and elderly people with AD are twice as likely to suffer from traumatic falls as their peers without AD (10). The effect of acupuncture treatment on the gait performance has been reported in neurodegenerative diseases and brain diseases (11, 12). Pereira et al. found that there were statistically significant differences between acupuncture group and sham-acupuncture group in the gait speed, gait cadence, left–right step length of patients with Parkinson disease, indicating that acupuncture could improve gait in Parkinson disease patients (11). Lou et al. found that step length, gait speed, step frequency, and ground reaction force impulse of stroke patients significantly increased after the acupuncture treatment, indicating that acupuncture could help to improve the gait performance of stroke patients (12). However, the effect of acupuncture on the gait performance has not been reported in AD patients.

Functional near-infrared spectroscopy (fNIRS) is an important tool used to evaluate the neurofunctional activity during walking because it allows to research cerebral hemodynamic activity in an ecological environment without strong immobility constraints (13). A systematic review showed that oxyhemoglobin (HbO_2_) levels within the prefrontal cortices were sensitive to compensation strategies reflecting postural control and gait disorder recovery (13). A study has demonstrated, using fNIRS, that HbO_2_ levels within prefrontal cortices were significantly increased while walking after acupuncture treatment in Parkinson disease patients, and may be sensitive to compensation for restoration of gait disturbance (14). However, fNIRS has not been reported to assess the effects of acupuncture for improving gait disturbance in AD patients.

Therefore, this study aims to assess the clinical effect of acupuncture on gait performance in AD patients and to examine the acupuncture effect on cerebral cortices by identifying hemodynamic changes that occur in the prefrontal cortices using the fNIRS technique.

## Methods

### Study design

This randomized controlled trial (RCT) will be performed in the Third Affiliated Hospital of Zhejiang Chinese Medicine University according to the Declaration of Helsinki. The subjects will be recruited from July 1 to December 31 in 2024 (by the recruitment posters), WeChat (the largest social media platform in China), and from the outpatient and ward of Neurology Department and Neurological Rehabilitation Department. Eligible patients will be randomly assigned to the acupuncture group and control group at the ratio of 1:1. This trial has been approved by the Ethics Committee of the Third Affiliated Hospital of Zhejiang Chinese Medicine University (approval number: ZSLL-KY-2023-015-01), and registered on the ClinicalTrials.gov (NCT06346275).^1^ Informed consent will be signed by each patient (Supplementary material 1). The flowchart is shown in Figure 1, and the timepoint of assessment is shown in Table 1.

**Figure 1 fig1:**
[figure not shown]
Flowchart of trial process.

**Table 1 tab1:** Study schedule of enrollment, intervention, and assessments.

	Enrollment	Allocation	Treatment	
Timepoint		0 day	4-week	8-week
Enrollment				
Eligibility screen	X			
Informed consent	X			
Demographics	X			
Previous medical history	X			
Routine blood	X			
Liver function	X			
Kidney function	X			
Electrocardiograph	X			
Magnetic resonance imaging	X			
Allocation		X		
Interventions				
Acupuncture group			X	X
Control group			X	X
Assessments				
Three-dimensional gait analysis		X	X	X
Cerebral hemodynamics		X	X	X
MMSE		X	X	X
MoCA		X	X	X
BI		X	X	X

MMSE, Mini-Mental State Examination; MoCA, Montreal Cognitive Assessment; BI, Barthel Index.

Patients’ information on demography, diagnosis and treatment history will be recorded, including birth date, gender, ethnicity, age, marital status, occupation, education level, height, weight, medical history, course of illness, treatment history, drug allergy history, and current concomitant medication. Patients are required to complete the laboratory tests, including blood routine, liver and kidney function, electrocardiogram, and magnetic resonance imaging.

### Study population

#### Diagnosis criteria

The diagnostic criteria of AD from Western medicine will be determined according to The National Institute on Aging-Alzheimer’s Association (NIA-AA) (15): (1) cognitive decline that affects daily life and includes damages to two or more cognitive domains; (2) early and most significant cognitive impairment belonging to the past phenotype or non-forgetting phenotype (language disorder, visual spatial disorder, or executive dysfunction); (3) excluding vascular dementia, Lewy body dementia, frontotemporal dementia, primary progressive semantic aphasia, and other active neurological disorders; (4) with biomarkers of brain amyloid-beta (Aβ) protein deposition.

The diagnostic criteria of AD from traditional Chinese medicine will be determined according to Chinese Internal Medicine (16): (1) onset symptoms, main symptoms: decreased ability to remember recent and distant events, cognitive decline (such as ability to judge people, objects, time, location, calculation ability, spatial recognition, language, etc.); accompanying symptoms: character changes such as withdrawn personality, indifferent expression, selfishness and narrowness, stubbornness, irrational euphoria, easy to get excited or angry, decreased understanding, and personality changes such as lack of morality and ethics, and lack of shame; (2) characteristics of onset: hidden onset, slow progression, and long course of disease; (3) syndrome of insufficient marrow-sea: memory loss, loss of recognition and calculation, dull expression, lifeless eyes, low and timid voice or silence all day; slow movement, tinnitus and deafness, withered auricula, hair loss and tooth shaking; red and thin tongue, white tongue moss, and weak pulse.

The dementia stage will be determined using Clinical Dementia Rating (CDR), which assesses cognitive and functional decline from 6 domains: memory, orientation, judgment and problem solving, community affairs, home and hobbies, and personal care (17). The dementia is divided into none (CDR = 0), questionable (CDR = 0.5), mild (CDR = 1), moderate (CDR = 2), and severe level (CDR = 3) (17).

#### Inclusion criteria

The inclusion criteria are as follows:

Aged 40–85 years old;Meeting the mentioned-above diagnostic criteria from traditional Chinese medicine and Western medicine;With mild to moderate dementia (CDR = 0.5, 1.0, or 2.0 points);Hachinski Ischemic Scale (HIS) ≤ 4 points;Hamilton Depression Rating Scale (HAMD) < 20 points;Without severe bone and joint diseases and able to walk independently;Able to conduct vision and hearing tests;Volunteering to participate in this trial and signing an informed consent form.

#### Exclusion criteria

The exclusion criteria are as follows:

Dementia caused by other systemic or neurological diseases, such as central nervous system infections, post-traumatic dementia, Parkinson’s disease dementia;Suffering from acute illness, upper limb extrapyramidal stiffness, neurological or psychiatric disorders (except cognitive impairment);With medical history that interferes with cognitive function assessment, such as past history of psychiatric drug abuse, drug addiction within the past 5 years, and alcohol abuse;Afraid of acupuncture and cannot accept acupuncture treatment;Currently participating in other clinical trial that affects the outcome evaluation of this trial.

#### Withdrawal criteria

Participants themselves requesting to withdraw from the trial;Participants experiencing serious adverse reactions during the trial that are not suitable to continue the trial;Participants experiencing serious complications or the condition worsens that require emergency measures during the trial, and unable to continue the treatment;Patients unable to continue observation due to transferring to another hospital for treatment.

### Randomization and allocation concealment

Prior to the commencement of the trial, we will utilize SPSS version 25.0 software (IBM Corp., Armonk, NY, USA) to generate a random sequence of numbers, allocating participants into two groups (A and B) with a 1:1 ratio. Group A represents the experimental group, while Group B serves as the control group. The random sequence and group allocation information will be securely stored and kept confidential by the principal investigator. We will prepare 108 opaque brown envelopes corresponding to the number of participants to be enrolled. Each envelope will be sequentially numbered on the exterior. Inside each envelope, we will place a sheet containing the corresponding random sequence number and group allocation information. The 108 envelopes will be randomly distributed to the clinical centers involved in the study. Participants will be strictly follow inclusion and exclusion criteria to determine eligibility. Upon confirmation of eligibility, a designated staff member will open the envelopes in ascending order of their numerical identifiers to reveal the group allocation.

### Blinding

Due to the particularity of acupuncture, it is difficult to blind clinical operators and participants. Patients will be informed of the treatment method after receiving grouping information. The efficacy evaluator will be blind. Cognitive function evaluation will be conducted by the researcher who is unaware of the allocation. Liver and kidney function and electrocardiogram testing will be completed by the inspector who is unaware of the allocation. The statistician will be blind when performing statistical analysis. The researchers, clinical operators, and efficacy evaluator are independent.

### Intervention

The control group will receive conventional drug therapy and cognitive rehabilitation therapy. The acupuncture group will receive acupuncture treatment based on the control group. The acupuncture operators are professional acupuncturists who have worked for more than 2 years.

#### Control group

##### Conventional drug therapy

The donepezil tablets (specification: 5 mg × 14 tablets, ZEN Biotechnology Co., Ltd., Chongqing, China) are taken before bedtime (5 mg/time, once a day). Basic treatments are adopted to control blood pressure, blood sugar, blood lipids, and improve brain metabolism.

##### Cognitive rehabilitation therapy

The cognitive training system (JZ-RZ-1020, Extreme Medical Technology, Hangzhou, China) will be used to help develop personalized rehabilitation plans for one-on-one training based on the cognitive function of each patient. The trainings include memory, hand eye reinforcement, attention, reaction. Patients are treated for 30 min each time and 5 times a week for 8 weeks.

#### Acupuncture group

The acupuncture treatment will be conducted based on the control group.

Acupoints: Baihui (GV20), Sishencong (EX-HN1), Fengchi (GB20), Taixi (KI3), Zusanli (ST36), Sanyinjiao (SP6), Neiguan (PC6), and Shenmen (HT7) (Supplementary material 2).

GV20 and EX-HN1: Patients are placed in a suitable position, and local disinfection is performed with 75% alcohol. The 28^#^ stainless-steel needles (Huatuo, Suzhou Medical Instruments Factory, China) will be used in this study with a size of 1.5 inches. When entering the needle, the needle body forms an angle of about 30° with the scalp. The needle tip points forward and enters the GV20, and needle in the EX-HN1 pointed to the GV20 direction. The needle is quickly pierced into the scalp, with a horizontal needling of 0.5 to 0.8 inches. When the resistance under the needle decreases, the needle body is inserted along the subgaleal area in the direction of the acupoint line. When patients achieve the Deqi sensation that characterized by a soreness, numbness, and distention, twisting and replenishing method is used and lasts for 2 min (200 times/min). The needle is left for 6 h, and the twisting and replenishing method is performed every 2 h during the needle retention period. The operation lasts for 1 min each time, for 3 times, until the needle is pulled out.

GB20, KI3, ST36, SP6, PC6, and HT7: Patients are placed in a supine position, followed by acupoints determination and disinfection, and 1.5-inch or 2-inch needle is used. The needle, toward the tip of the nose, is obliquely inserted into GB20 with a depth of 0.8–1.2 inches, and twirling reinforcing-reducing method is used. The needle is obliquely inserted upwards into PC6 with a depth of 1–2 inches, and directly inserted into HT7 with a depth of 0.3–0.5 inches and into KI3 with a depth of 0.5–0.8 inches. The needle, slightly tilted toward the tibia, is directly inserted into ST36 with a depth of 1–2 inches. SP6 is directly needled with a depth of 1–1.5 inches. The twisting and replenishing method is used for limb acupoints, and needles are left for 30 min. The operation when starting the needle is standard to prevent bleeding and hematoma.

To ensure the uniformity of operations, the acupuncture sequence for EX-HN1 is front, back, left, and right. The acupoints on both sides are first punctured on the left side, and then on the right side. Acupuncture treatment is performed once a day (five times a week) and lasts for 8 weeks.

### Follow-up

Both the experimental and control groups will undergo continuous treatment for 8 weeks. Assessments of relevant indicators will be conducted by designated personnel at three time points: before treatment, after 4 weeks, and after 8 weeks of treatment. Additionally, participants will be followed up within 1 month after completing the treatment. Each assessment will take place in a private room, allowing family members to participate in the evaluation process.

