### Data management and quality control

Quality control: (1) Unified technical training for researchers. The content includes familiarizing with the objectives and requirements of this study, mastering relevant diagnostic and treatment standards, random allocation methods, acupuncture methods, and the use of evaluation forms.

(2) Strict record and summarization of this clinical trial. A uniformly printed Case Report Form (CRF) will be adopted, with unified numbering and registration of allocation. Researchers conduct the trial strictly following the project design plan, and carefully and objectively filling out the CRF.

(3) Real time monitoring during the trial. A dedicated quality monitoring team will be established, which will be charged by the principal researcher, who is responsible for verifying whether the researchers have followed the trial protocol and whether the CRF has been filled out in a timely and accurate manner.

(4) Strengthening the compliance. Researchers make patients fully know about the purpose and significance of the study, sign an informed consent form, and provide free treatment and related examinations.

Data management: the CRF is completed in a timely and accurate manner, and then handed over to a dedicated data entry personnel for data storage after inspection by the quality inspector.

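### Letting family members take part in every assessment puts the promised evaluator blinding at risk, mainly for MMSE, MoCA and BI

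*Protocol article*

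**What the plan says.** The Follow-up section provides for assessments before treatment, after 4 weeks and after 8 weeks, and then states: "Each assessment will take place in a private room, allowing family members to participate in the evaluation process".

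The Blinding section accepts that operators and patients cannot readily be blinded, and says of patients: "Patients will be informed of the treatment method after receiving grouping information". It then promises three kinds of blinding that bear on efficacy:
- evaluator: "The efficacy evaluator will be blind"
- cognitive rater: "Cognitive function evaluation will be conducted by the researcher who is unaware of the allocation"
- statistician: "The statistician will be blind when performing statistical analysis"

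It adds that researchers, operators and evaluator are independent of one another.

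The Intervention section describes an add-on comparison. Both arms receive drug therapy and cognitive training, and one arm also receives acupuncture. No sham procedure is described.

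Three further statements touch on blinding:
- Data management and quality control: "A uniformly printed Case Report Form (CRF) will be adopted, with unified numbering and registration of allocation"
- Randomization and allocation concealment: "Group A represents the experimental group, while Group B serves as the control group"
- Acupuncture group, on the scalp points: "The needle is left for 6 h"

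**The concern.** With patients and operators aware of the arm and no sham, masking of the evaluator is the main protection for outcomes that depend on a rater or on how a test is conducted. The Follow-up rule brings into each assessment people who very likely know the treatment, gives them a part in the evaluation, and sets no limit on that part.

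Two kinds of harm are possible. First, a relative may mention the treatment, and the evaluator is then no longer blind. Second, a relative may help. MMSE and MoCA are performance tests scored from the patient's own answers, so a hint changes the score even if the rater stays blind. BI describes daily function. A relative can sensibly inform it, but one who knows the arm and hopes for benefit may report differently.

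These outcomes carry the trial's cognitive aim, as stated in the Abstract and Discussion. Bias of this kind cannot be removed once the assessments are done.

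**Working it through.** **Setting the sections side by side**

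1. *Do family members know the arm?* The article does not say so. It follows with high likelihood from three stated facts: the patient is told the treatment, only one arm is needled, and needling takes place five times a week for 8 weeks (5 × 8 = 40 sessions).
2. *Does the rule reach the outcome assessments?* Yes. It covers each assessment, and the family's part is to participate, not merely to accompany or wait.
3. *Is there a counter-rule?* None is stated. Nothing limits the family's role or asks family or patients to keep the treatment from the evaluator.
4. *Which outcomes are exposed?*
   - MMSE and MoCA: prompting and disclosure.
   - BI: disclosure and informant bias.
   - Gait and HbO2: recorded by motion capture and fNIRS, so rater judgement matters less. Instruction and encouragement during the walking tasks remain a smaller route.
   - Animal naming: only the concurrent load in the second dual task. It is not listed as an outcome.

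**The plan's own figure**

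The point does not depend on the sample size, but the illustration below uses it, so it was reproduced from the Sample size estimation section.
- Difference: 121.76 − 115.76 = 6.00 steps/min.
- Pooled SD: √[(9.59² + 10.04²)/2] = 9.82.
- Two-sided α = 0.05, power 0.80: n = 2(1.960 + 0.842)² × 9.82²/6.00² ≈ 42.1, so 43 per arm. The exact t test gives 43.01, with power 0.7999 at n = 43.
- Dropout: 43/0.80 = 53.75, so 54 per arm and 108 in total.

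The stated 43, 54 and 108 are confirmed. Better blinding would not change them.

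**Illustration of what a shift would do**

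Assume no true effect and a between-arm shift of δ SD caused only by prompting or disclosure. The two-sample t statistic then has noncentrality δ√(n/2), and the two-sided 5% test rejects as follows.

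| Assumed shift δ (SD) | δ√(43/2) | Rejection rate, 43 per arm | Rejection rate, 54 per arm |
|---|---|---|---|
| 0 | 0 | 5.0% | 5.0% |
| 0.1 | 0.46 | 7.4% | 8.1% |
| 0.2 | 0.93 | 15.0% | 17.8% |
| 0.3 | 1.39 | 28.0% | 33.9% |

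The values of δ are assumptions. Nothing in the article supports any one of them.

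**The case against.** Allowing family to participate is not the same as letting them answer, prompt or disclose. The trial admits patients up to CDR 2, for whom some family presence is reasonable, and an informant is useful for BI. Family may attend in both arms, so help given equally would not bias the comparison. The primary outcomes are instrument-recorded, and the article already declares the lack of patient and acupuncturist blinding as a limitation.

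Much of this stands. It limits the reach of the point to mainly secondary outcomes and makes the size of any bias unknown. It does not remove the conflict. The rule is affirmative, covers every assessment and stands beside a promise of blind evaluation with nothing to protect it. The declared limitation concerns acupuncturists and patients, not the evaluator. Family who know the arm also have reason to behave differently by arm.

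A reader might go further and infer that the plan undoes its own blinding in several places. The article does not support that:
- **CRF.** Allocation is registered on it, but the text does not say that evaluators see or complete that entry. The word researcher is used both for the blinded cognitive rater and for those who fill out the form, which leaves a doubt but proves nothing.
- **A/B codes.** Group A is fixed as experimental, but nothing says the analysis file carries those labels. The sequence is held in confidence by the principal investigator.
- **Needles.** Scalp needles stay in place for hours on treatment days, but no assessment is scheduled while they are in place, and five sessions a week leave days without treatment.

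These are operational details that an article may leave to the full protocol or analysis plan.

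**Conclusion.** The point holds for the family rule. The Follow-up section, followed as written, puts the evaluator blinding promised in the Blinding section at risk and lets prompting affect MMSE and MoCA, and disclosure or informant bias affect BI. It should be corrected, but it does not show that blinding fails or that the primary outcomes are compromised.

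The conclusion rests on one inference, that family will usually know the arm. A biased comparison further requires that disclosure or help differs between arms, which is plausible but not shown. The magnitude cannot be determined from the documents. The rates of about 7%, 15% and 28% show only how the 5% error rate would respond to assumed shifts of 0.1, 0.2 and 0.3 SD at 43 per arm. The CRF, coding and needle questions are reasons for inexpensive safeguards, not demonstrated errors.

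**What to change.** **Main change (Follow-up section).** State that:
- family members do not take part in the MMSE, MoCA or gait/fNIRS test sessions;
- family act only as informants for BI;
- family and patients are told before each assessment not to reveal the treatment to the evaluator.

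**Safeguards worth adding (not corrections of proven errors).**
- Keep allocation off the CRF pages that evaluators see, for example on a separate form.
- Give the statistician neutral codes instead of A and B, with the key held by someone else until the analysis is locked.
- Book the week-4 and week-8 assessments for times when no needles are in place. This concerns the assessment appointment only and leaves the treatment schedule as it is.

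**Cost.** Protocol wording, possibly a reprinted CRF page, and some appointment planning. No extra patients or staff are needed, and the sample size is unchanged. The small downside is that some patients may be less at ease without a relative in the room.
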